#### Statistical Analysis

Sociodemographic data will be descriptively analyzed (mean, standard deviation, percentage, range). Normality will be tested for all quantitative variables. The characteristics of participants of both groups will be compared via a *t* test or a Mann-Whitney test for nonnormally distributed variables. An intention-to-treat analysis will be adopted; data from all included patients will be analyzed even if they withdraw. Independent sample *t* tests for group differences (or Mann-Whitney U tests for nonparametric data) will be used to evaluated differences in endpoints between pre- and postintervention data. Analysis will be carried out using multiple imputation if some participants have withdrawn from the study before the eighth week. Analyses will be performed using RStudio software.

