**Methods:**

This is a serial, comparative, randomized controlled group study. Both groups (n=25 in each) will receive psychomotor rehabilitation care. However, the methods of delivery will be different; one group will be exposed to the Medimoov exergame platform, and the other only to traditional means of psychomotor rehabilitation. The selection criteria will be (1) age of 65 years or older, (2) ability to answer a questionnaire, (3) ability to stand in a bipedal position for at least 1 minute, (4) score of 13 or greater on the Short Fall Efficacy Scale, and (5) stable medical condition. An evaluation will be made prior to starting the intervention, after 4 weeks of intervention, and at the end of the intervention (after 8 weeks), and it will focus on (1) risk of falls, (2) fear of falling, and (3) cognitive evaluations. Physical activity outside the session will also be assessed by actimetry. The outcome assessment will be performed according to intention-to-treat analysis.

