### Participants and Recruitment

The research project will be conducted in two intermediate-care wards for older adults at the Charles Foix Hospital, a French geriatric hospital. Guidelines to calculate the sample size do not exist in the literature yet; thus, the sample size has been estimated based on previous studies evaluating fear of falling–focused interventions [28,29]. A sample size of 20 participants per group is often reported. A total of 25 participants per group will be recruited to factor in a potential 20% withdrawal or other variations. Recruitment will be conducted among hospitalized patients in intermediate-care rehabilitation hospital wards. The inclusion criteria will be as follows: (1) age of 65 years or older, (2) ability to understand and answer short and simple questions (as determined by the clinical interview), (3) ability to stand upright in a bipedal position, feet together, for longer than 1 minute with or without a technical aid, (4) a score of 13 or greater on the FES-I [30] (moderate or severe fear of falling), (5) stable medical condition, and (6) ability to give written consent. The exclusion criteria will be as follows: (1) cannot correctly distinguish the elements on the screen, (2) in palliative care, (3) under a legal protection measure, (4) obtained a score <16 on the Mini Mental State Examination (MMSE) [31], and (5) recently underwent orthopedic surgery (<2 months); the latter is an exclusion criterion because it requires specific rehabilitation programs [32]. The MMSE will be used for screening purposes only to exclude patients with severe cognitive disorders that would prevent them from participating. Participation may be interrupted at the participant’s request or if the participant experiences an adverse health event (eg, stroke). All patients hospitalized in the rehabilitation ward at the beginning of the study will be screened for eligibility by their physicians, and if eligible, will be asked to participate after a detailed presentation of the protocol by a postdoctoral fellow or a research professional. The eligibility of the patients admitted to hospital after the start of the study will be verified. Participant recruitment will be ongoing until the sample number (N=50) is reached. Eligible patients will receive a letter of information. A random selection will be conducted if the number of eligible patients is higher than the number of required participants.

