#### Endpoints

The primary clinical endpoint is the comparison of the changes in FES-I scores between the two groups. The main secondary endpoint is the comparison of changes in TUAG scores between the groups. Other secondary endpoints are a significantly greater improvement in the One-Leg Stand test, the SPPB test, the Trail Making Test Parts A and B, and the Stroop test in the intervention group and a high level of satisfaction in the intervention group.

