### Strengths and Limitations

One of the strengths of the study is that it follows the SPIRIT guidelines [26,27] and the PEDro recommendations [33]. It ensures internal and external validity and provides the necessary information to interpret the results of this study. Another strength is the comparison to the standard in rehabilitation for fall prevention in the context of French geriatric hospitals. Regarding outcome measurement, standardized measures have been chosen based on their sensitivity to change [40] to highlight the effect of the intervention. Moreover, results regarding the intervention effectiveness are assessed with standardized scales and with accelerometers, ensuring data triangulation.

This protocol also presents some limitations. Due to the nature of the intervention, double blinding is not possible. However, measures of the outcomes will be blinded and performed by trained assessors to minimize bias. Moreover, stratification on age, gender, fear of falling, and risk of falls will not be possible for the randomization, as the participants will not all be identified at the beginning of the study. However, possible differences between groups at baseline will be tested to consider them in data interpretation. Desirability bias can occur with participants trying to please the assessor. This bias will be the same in both groups. To minimize this bias, primary and secondary outcomes will be assessed by an independent assessor (different from the psychomotor therapist administrating the intervention). This is an exploratory study with significant limitations in terms of sample size, power, and hence, depth of the statistical analysis that can be conducted. However, in the context of a future larger trial (if warranted), an appropriate sample size and power calculation will be undertaken, which would also allow for a more detailed and robust statistical analysis of the data with enhanced validity and integrity of the results.

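### The primary Short FES-I comparison uses unadjusted pre-post differences and a data-chosen test; one prespecified baseline-adjusted model would be modestly more precise and would fix the reported quantity

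*Protocol article*

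**What the plan says.** - **Endpoint (Endpoints).** "The primary clinical endpoint is the comparison of the changes in FES-I scores between the two groups". Change in TUAG is the main secondary endpoint.
- **Test (Statistical Analysis).** Group differences are assessed by independent-sample t tests, with the alternative "or Mann-Whitney U tests for nonparametric data) will be used to evaluated differences in endpoints between pre- and postintervention data". No regression, ANCOVA or mixed model is named, and no baseline covariate.
- **Choice of test (Statistical Analysis).** "Normality will be tested for all quantitative variables". Neither the normality test nor a threshold is given.
- **Withdrawals (Statistical Analysis).** Intention to treat, with multiple imputation for participants who leave before week 8.
- **Baseline imbalance (Strengths and Limitations).** Stratified randomization is ruled out, and "possible differences between groups at baseline will be tested to consider them in data interpretation".
- **Size (Participants and Recruitment).** "A sample size of 20 participants per group is often reported", and "A total of 25 participants per group will be recruited to factor in a potential 20% withdrawal or other variations".

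The description of the TUAG test also calls TUAG the primary outcome. That conflict is a separate matter. This point follows the Endpoints section and takes Short FES-I as primary.

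**The concern.** Short FES-I is measured at baseline in everyone. Subtracting it uses that information with the slope fixed at 1, while a model with baseline as covariate estimates the slope. Three things follow.

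1. If the true slope is below 1, the change score carries avoidable variance, in a trial that describes its own power as limited.
2. A chance difference in baseline Short FES-I is over-corrected by subtraction and moves the estimate. The plan's only response is a baseline significance test followed by narrative. With allocation blocked but not stratified, adjustment in the model is the natural way to deal with this.
3. If normality testing selects the test, the primary result may be a difference in means or a rank comparison, and which one is unknown until the data are seen. Under multiple imputation the check could pass in some completed data sets and fail in others. The plan names no rank-based estimate and standard error to pool.

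**Working it through.** **Inputs from the protocol article.** 20 per group before and 25 after a 20% withdrawal allowance; Short FES-I entry score of 13 or more; Short FES-I 4-week test-retest ICC 0.83; TUAG 2-week ICC 0.93 to 0.99; community-dwelling mean Short FES-I of 15 (Introduction).

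**Assumed.** The correlation r between baseline and week 8 is not given. The ICC of 0.83 is a likely upper bound over 8 weeks of treatment, so I use 0.5 to 0.83. Pre and post SDs are taken as equal (1 unit). Parent SD is 5.

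**The plan's own figure.** 20/(1 - 0.20) = 25 per group, which reproduces. The 20 comes from precedent, so there is no power calculation to check.

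**Precision without truncation.** Per-person variance is 2(1 - r) for a change score and 1 - r² after baseline adjustment, so the ratio is (1 + r)/2. Estimating the slope multiplies this by about 1 + 1/(2n - 4) = 1 + 1/46 = 1.022 at n=25 per arm.

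| r | (1+r)/2 | with slope cost | simulated, 25 per arm |
|---|---|---|---|
| 0.5 | 0.75 | 0.77 | 0.755 |
| 0.7 | 0.85 | 0.87 | 0.874 |
| 0.83 | 0.915 | 0.935 | 0.926 |

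The saving is therefore about 7% at r=0.83 and 23-25% at r=0.5. At 20 completers per arm the slope factor is 1 + 1/36 = 1.028 and the picture is almost the same (simulated 0.779, 0.878 and 0.929).

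**Precision with the entry floor.** A floor of 13 on a parent mean of 15 and SD of 5 truncates at (13 - 15)/5 = -0.4 SD. With λ = φ(0.4)/Φ(0.4) = 0.3683/0.6554 = 0.562, the baseline variance falls to 1 - 0.4 × 0.562 - 0.562² = 0.46. Change-score variance is then (1 - r)² × 0.46 + (1 - r²), and adjusted variance stays at 1 - r².

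- r=0.5: 0.75/(0.115 + 0.75) = 0.867; × 1.022 = 0.89
- r=0.7: 0.51/(0.041 + 0.51) = 0.925; × 1.022 = 0.945
- r=0.83: 0.3111/(0.0133 + 0.3111) = 0.959; × 1.022 = 0.98

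Simulations gave 0.88-0.90 at r=0.5 and 0.97-0.98 at r=0.83. The saving is about 2-12%.

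**TUAG.** At r = 0.93 to 0.99, (1 + r)/2 = 0.965 to 0.995; × 1.022 = 0.99 to 1.02. Break-even is at r = 2/1.022 - 1, about 0.96. Above that, adjustment costs slightly more than it saves.

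**Chance imbalance.** A baseline difference of 0.5 SD at 25 per arm gives t = 0.5/√(2/25) = 1.77 on 48 df, p = 0.083, so a 5% test would not flag it. It shifts the change-score estimate by (1 - r) × 0.5, which is 0.085 SD at r=0.83 and 0.25 SD at r=0.5.

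**Normality gate.** If the check were run in each arm at 5% (assumed, since the article does not say), normal data would be sent to Mann-Whitney in 1 - 0.95² = 9.75% of trials by chance alone.

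**The case against.** The strongest reply is that nothing here is an error. The endpoint is defined as a comparison of changes, the test compares changes, and randomization makes it valid. The authors call the study exploratory and defer fuller analysis to a larger trial. All of that stands: the point is about efficiency and a fixed estimate.

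A reader might infer more than the document supports:

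- *That the planned test is biased or ignores baseline.* Baseline is subtracted. The shift from imbalance is conditional on the allocation obtained and averages out over randomizations.
- *That a change score can never beat baseline adjustment.* At this sample size it can, once r exceeds about 0.96, which lies inside the reliability range quoted for TUAG.
- *That the loss is large.* A saving of a quarter of the variance, or a 0.25 SD shift, needs r near 0.5 with no entry floor. The only Short FES-I figure in the article is 0.83, and the floor of 13 shrinks the gain further.
- *That TUAG loses power for want of adjustment.* The quoted reliability points to about nil. Any benefit from a log scale would be a different matter and would rest on a skew that the article does not give.
- *That Mann-Whitney cannot be combined with multiple imputation.* It has an associated estimate, U/(n1·n2), with a variance. The fair criticism is that the plan does not name it.

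Selection by a normality test is the natural reading of the text, not a rule spelled out there. The use of week-4 scores, a ward covariate and the contents of the imputation model are details or preferences that an article may leave elsewhere, and are not part of this point.

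**Conclusion.** The point holds as a modest improvement. The article fixes an unadjusted comparison of changes, so this is a stated choice and not a detail left to an unseen analysis plan. For Short FES-I, baseline adjustment would lower the variance by about 7% (r=0.83) to 23-25% (r=0.5) without truncation. With the entry floor it would be about 2-12% over the same range. These figures rest on an assumed r, equal pre and post SDs and, for the floor, a parent mean of 15 and SD of 5. The case for a single prespecified model, in place of a data-chosen test, does not depend on r. It concerns which quantity will be reported and how it is pooled over imputations.

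**What to change.** Name one primary analysis: a linear model of week-8 Short FES-I on group with baseline Short FES-I as covariate. Fit it in each imputed data set, pool by Rubin's rules, and report the adjusted difference with its 95% CI. The endpoint can still be described as change, because regressing change on group and baseline gives the same group coefficient. Remove the normality-driven choice of test and keep a rank test as a sensitivity analysis. Baseline tests are then no longer needed to deal with Short FES-I imbalance.

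The cost is a few lines of analysis text and R code, with no new data. The article reports 10 of 50 participants enrolled and no analyses begun, so at that stage the change could still be prespecified.

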## Results

The study received funding in February 2020. As of October 2020 (submission date), and due to the context of the COVID-19 pandemic, a total of 10 participants out of 50 have been enrolled in the study. The projected date for the end of the data collection is December 2021. Data analyses have not started yet, and publication of the results is expected for Spring 2022.

## Discussion

### Principal Considerations

This study will allow us to evaluate the effect of psychomotor rehabilitation using the Medimoov interactive gaming platform on fear of falling and risk of falls. Most exergames do not allow for the personalization of the games according to the patient’s abilities, which is essential in rehabilitation [53]. An original aspect of Medimoov is that it provides multiple options to personalize each game and follows the progression of the participants; evaluating the effectiveness of this platform will thus provide new rehabilitation perspectives. Moreover, the study by Lister et al (2014) [16] shows that gamification in health often does not follow professional guidelines and recommendations, which leads to mixed results on fear of falling and risks of falls across studies [17,21]. The design of the present study takes into consideration the recommendation of Lister et al (2014), and we will rigorously compare two rehabilitation programs (the program with the Medimoov platform and the traditional psychomotor therapy sessions) that follow the French national guidelines on fall prevention [13]. Thus, this study will address gaps in the literature and will provide knowledge on patient-personalized exergame effectiveness, which has strong potential for practice and policy changes.

Exergames are often considered to facilitate older adults’ motivation to participate in rehabilitation programs [19-21,54]. This study will allow us to explore this assumption and compare participant adherence across groups. The results of this study will, therefore, offer new perspectives on fall prevention programs with effects on both fear of falling and risks of falls, with increased motivation and adherence from the older adult. In addition, links between actimetry and clinical data for this specific population will be explored. The study by Pereira et al (2014) [10] demonstrated that being active (at least 1125 metabolic expenditure minutes per week) was correlated with a decreased risk of falls [10]. The measurement of actimetry has been shown to be an accurate representation of older adults’ motor activity [55]. However, the use of actimetry to measure physical activity has limitations; certain activities may not be measured properly depending on where the device is worn on the body (eg, wrist, waist) [55]. Moreover, the removal of the device can sometimes be interpreted as a period of inactivity [55]. This latter limitation will be mitigated through the collaboration of the hospital’s care staff, who will notify the research team in the event of any removal of the device. Measuring the evolution of the older adults’ actimetry during and after their rehabilitation program will help develop further knowledge on rehabilitation programs, which has the potential to provide older adults with more adapted rehabilitation programs and decrease the incidence of falls [5].

### Strengths and Limitations

One of the strengths of the study is that it follows the SPIRIT guidelines [26,27] and the PEDro recommendations [33]. It ensures internal and external validity and provides the necessary information to interpret the results of this study. Another strength is the comparison to the standard in rehabilitation for fall prevention in the context of French geriatric hospitals. Regarding outcome measurement, standardized measures have been chosen based on their sensitivity to change [40] to highlight the effect of the intervention. Moreover, results regarding the intervention effectiveness are assessed with standardized scales and with accelerometers, ensuring data triangulation.

This protocol also presents some limitations. Due to the nature of the intervention, double blinding is not possible. However, measures of the outcomes will be blinded and performed by trained assessors to minimize bias. Moreover, stratification on age, gender, fear of falling, and risk of falls will not be possible for the randomization, as the participants will not all be identified at the beginning of the study. However, possible differences between groups at baseline will be tested to consider them in data interpretation. Desirability bias can occur with participants trying to please the assessor. This bias will be the same in both groups. To minimize this bias, primary and secondary outcomes will be assessed by an independent assessor (different from the psychomotor therapist administrating the intervention). This is an exploratory study with significant limitations in terms of sample size, power, and hence, depth of the statistical analysis that can be conducted. However, in the context of a future larger trial (if warranted), an appropriate sample size and power calculation will be undertaken, which would also allow for a more detailed and robust statistical analysis of the data with enhanced validity and integrity of the results.

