### Randomization

After the randomization, patients will be allocated to an intervention group (rehabilitation program with the Medimoov platform) or to a control group (traditional psychomotor therapy sessions). The randomization will be conducted directly after the signature of the consent form. To ensure concealed allocation [33], each participant will be assigned a code used for the randomization. As the participants will not all be identified before the randomization, block randomization will be conducted (rather than stratification) to control the sample size of each group using the “blockrand” function of RStudio software (RStudio PBC).

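### Stratification is ruled out for a reason that does not hold, and the fallback of testing baseline differences corrects nothing; adjust the primary comparison for baseline Short FES-I

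*Protocol article*

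**What the plan says.** The Randomization section sets blocks against strata: "As the participants will not all be identified before the randomization, block randomization will be conducted (rather than stratification"). Strengths and Limitations repeats the position, stating that "stratification on age, gender, fear of falling, and risk of falls will not be possible for the randomization", and gives the same reason: "as the participants will not all be identified at the beginning of the study". The remedy offered there is that "possible differences between groups at baseline will be tested to consider them in data interpretation".

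Four other statements bear on this:
- Participants and Recruitment makes "a score of 13 or greater on the FES-I" an inclusion criterion and places the trial in "two intermediate-care wards for older adults at the Charles Foix Hospital". Recruitment is rolling: "Participant recruitment will be ongoing until the sample number (N=50) is reached".
- The Randomization section has each patient allocated straight after signing consent.
- Table 1 and Study Procedures put the first Timed Up and Go, SPPB and other assessments in week 1, after allocation.
- Endpoints names the between-group comparison of change in FES-I as primary. Statistical Analysis tests pre-post differences with an independent-samples t test or a Mann-Whitney test and names no covariate.

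**The concern.** Blocking and stratification are not alternatives. Stratified block randomisation keeps one block list per stratum, and each arriving patient takes the next place on the list for their stratum. No roster of future participants is needed, so rolling recruitment is no obstacle. The article therefore presents a design choice as an impossibility. Because its Conclusions describe this pilot as the basis for larger trials, the mistaken reason could be carried forward.

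The practical question is what protects the primary comparison from chance imbalance in baseline fear of falling. A significance test at baseline does not alter the estimate, and with 25 per arm it has little ability to pick out an imbalance worth having adjusted for. The planned analysis of change scores removes only part of such an imbalance, because the arm that starts worse tends to regress further.

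**Working it through.** **The plan's own figure.** The sample size starts from the statement "A sample size of 20 participants per group is often reported" and allows for 20% withdrawal: 20/(1 − 0.20) = 25 per group, 50 in total. This reproduces.

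**Which factors are known at randomisation.**

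| Factor | Known at consent? | Source |
|---|---|---|
| Age | Yes, eligibility criterion | Participants and Recruitment |
| Fear of falling (screening FES-I) | Yes, eligibility criterion | Participants and Recruitment |
| Gender | Yes, evident at enrolment | – |
| Ward | Yes, two wards (not among the factors the article lists) | Participants and Recruitment |
| Risk of falls (Timed Up and Go) | No, week 1, after allocation | Table 1, Study Procedures |

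Three of the four factors declared impossible were available. The fourth was not, but because of the assessment schedule and not for the reason given.

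**How often a baseline imbalance arises.** With 25 per arm the standardised baseline difference has standard error √(2/25) = 0.283.
- P(|difference| ≥ 0.4 SD) = P(|Z| ≥ 0.4/0.283 = 1.414) = 0.157.
- P(|difference| ≥ 0.5 SD) = 0.077.
- With 20 completers per arm, these become 0.206 and 0.114.

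**What the baseline test would show.** At 0.4 SD, t = 1.414 on 48 degrees of freedom, p = 0.164. To reach p < 0.05 the difference must exceed about 0.57 SD.

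**Effect on the change-score estimate.** Let r be the pre-post correlation, with equal SDs before and after. A baseline difference d carries an expected follow-up difference of r·d, so the difference in change shifts by (1 − r)·d in size.
- r = 0.83, the 4-week test-retest value in the FES-I section, used here as a stand-in: 0.17 × 0.4 = 0.068 SD.
- r = 0.5, assumed: 0.50 × 0.4 = 0.20 SD.

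The entry cut-off of 13 restricts the range of baseline scores, so a correlation below 0.83 is plausible.

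**Precision.** The change-score variance is proportional to 2(1 − r) and the baseline-adjusted variance to 1 − r², so their ratio is 2/(1 + r).
- r = 0.83: 2/1.83 = 1.09, so the change score has 9% more variance.
- r = 0.5: 2/1.5 = 1.33, so it has 33% more.

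**What stratification would add.** Simulation of 20,000 trials with patients arriving one at a time (assumed: blocks of 4, wards 50:50, fear-of-falling score cut at its median):

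| Scheme | Baseline FES-I difference ≥ 0.4 SD | Arm totals differ by ≥ 6 |
|---|---|---|
| Unstratified blocks | 15.2% | 0% |
| Ward × FES-I category (4 cells) | 2.6% | 0.4% |
| 16 cells | 5.7% | 17.4% |

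Every scheme ran without an advance list, which confirms that the stated obstacle does not exist. The last row shows that fine stratification is unsuitable for 50 patients.

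**The case against.** The strongest reply is that unstratified block randomisation is a valid design. Chance imbalance is not bias, and the error rate of the unadjusted test already allows for it. The article lists the lack of stratification as a limitation and calls the study exploratory. All of this stands.

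A reader might go further than the documents allow in three ways.
- **That the whole imbalance passes into the treatment estimate.** It does not. The endpoint is a change score, so only the fraction (1 − r) enters.
- **That the two wards must be balanced.** If they contribute 25 patients each (assumed), a ward splits 15:10 or worse in 26% of trials. The matching figure, arm shares at least 20 percentage points apart, is 15% for a 20:30 split and 22% for 15:35. But nothing in the article shows that ward is prognostic: both are intermediate-care wards of one hospital with the same session schedule. Even an assumed ward effect of 0.3 SD would move the estimate by only 0.20 × 0.3 = 0.06 SD.
- **That the trial should have stratified on all four listed factors.** Risk of falls is measured too late, and two levels of each factor would make 16 cells, too many for this sample.

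It is also fair to say that the article sets no p < 0.05 gate for acting on a baseline difference. The p-value of 0.16 therefore shows how uninformative the test is; it does not predict what the investigators would conclude.

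None of this rescues the stated reason, and it does not make baseline testing a substitute for adjustment.

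**Conclusion.** The rationale in both sections is wrong and should be corrected; that conclusion needs no assumption. The comparison is not biased by the absence of strata, and the documents do not support calling the randomisation defective.

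What is lost is precision and protection against an unlucky draw. About one trial in six (16%) would start with a FES-I imbalance of 0.4 SD or more. An imbalance of 0.4 SD distorts the change-score result by 0.07 SD at r = 0.83 and 0.20 SD at r = 0.5, and the unadjusted change-score analysis carries 9% to 33% more variance than a baseline-adjusted one. These sizes assume 25 analysed per arm, equal SDs before and after, and a correlation between 0.5 (assumed) and 0.83 (the article's test-retest value, taken as the pre-post correlation). The effect is modest, but it can be removed at little cost.

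**What to change.** 1. **Primary analysis.** Replace the unadjusted test of change in FES-I with a linear model (ANCOVA) of week-8 Short FES-I on arm and baseline Short FES-I, in all 50 participants, keeping the planned multiple imputation for withdrawals. State which score is the baseline: the screening score precedes allocation, the week-1 score follows it in Table 1. If residuals are clearly non-normal, give a robust or rank-based version as a sensitivity analysis.
2. **Baseline table.** Present baseline values by arm descriptively and drop the significance tests.
3. **Rationale.** In Randomization and in Strengths and Limitations, say that stratification was not used by choice, given the small sample, and that risk of falls is measured after allocation. Remove the claim that it was impossible because participants were not all identified in advance.
4. **Optional.** Stratify the remaining allocations on one factor, such as screening FES-I category, with one block list per level.

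Cost: items 1 to 3 need a text change before analysis, which the article says had not begun. Item 1 gives up the simple choice between a t test and a Mann-Whitney test, since the latter has no equally simple adjusted form. Item 4 needs an amendment, may leave arm sizes slightly unequal, could reach at most 40 of 50 patients at the October 2020 submission (10 already enrolled), and adds little once baseline is in the model. It lapses if enrolment has closed.
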